The number of patients who were screened as having AFib and had an abnormal ECG reading will be compared by using the participant’s medical record on Epic Systems. The number of positive screens versus negative screens will also be compared to assess the sensitivity and specificity of testing in the given population.

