## Results

As of March 1, 2024, a total of 2339 participants have been enrolled. Of the 6 UF Health specialty clinics, 335 were from the UF Health Nephrology Clinic, 466 from the UF Health Sleep Clinic, 597 from the UF Health Ophthalmology Clinic, 526 from the UF Health Urology Clinic, 231 from the UF Health Neurology Clinic, and 184 from the UF Health Pre-Surgical Clinic. The participants’ ages ranged from 18 to 99 years, with an average age of 61 (SD 10.25) years. The average weight of all participants is 194 (SD 14.26) lbs. The race distribution was reported to be 266 (11.42%) African American, 51 (2.18%) Asian, 124 (5.30%) Latino, 1818 (77.73%) White, and 80 (2.61%) others.

The KardiaMobile rhythm strip reported 381 abnormal readings, which are pending analysis from a cardiologist. A total of 78 readings were labeled as possible AFib, 159 readings were labeled unclassified, and 49 were unreadable. Additionally, 1573 (67.25%) of participants report not regularly seeing a cardiologist.

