## Discussion

A total of 2339 participants across 6 different medical specialty clinics were enrolled in this study. Preliminary findings of the feasibility and accuracy of performing routine cardiac rhythm sampling in patients deemed at high risk for AFib were encouraging, with the average length of patient enrollment being 3:30 (SD 0.5) minutes after informed consent was completed. This time included the participant filling out the site-specific questionnaire. The average length of the single-lead mobile ECG data collection was just 30 (SD 2.5) seconds. Furthermore, when considering feasibility, there were no reports from clinical staff regarding the patient enrollment effort impacting the flow of clinic operations, and 9 of 10 reported satisfaction with the study on clinic operations per medical staff (n=25). Regarding accuracy, the study demonstrated KardiaMobile to have a sensitivity and specificity of 95% and 97%, respectively, for detecting previously undiagnosed AFib. The relatively short time to collect the single-lead ECG along with the accuracy of the technology in detecting AFib suggests that the implementation of routine rhythm sampling with high-risk patients can be used cost-effectively in an outpatient clinic without increasing the time it takes for the patient to be seen by a physician.

The use of a single-lead mobile ECG strip can serve as a low-cost, effective AFib screen for implementation across outpatient clinics attempting to provide increased health care accessibility. A study published in 2022 suggested an “incremental cost-effectiveness ratio of US $57,894 per quality-adjusted life year, meeting the acceptability threshold of US $100,000 per quality-adjusted life year” regarding the cost-effectiveness of single-lead mobile ECGs [26,27]. Additionally, patients can easily purchase this device on their own and measure their ECG signal from the comfort of their own homes. This may allow for more immediate feedback on their heart health and a reduction in costs from clinic visits.

Limitations to the study include the fact that the study was not designed to measure the impact of potential moderators on the outcomes. Additionally, there were limitations related to the relatively high rates of unclassified or unreadable ECG outputs that have been included in the abnormal findings data. Furthermore, the participants were not asked to return for another reading, as these outputs are representative of the device’s effectiveness.

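### More than half of the 381 abnormal readings are strips with no rhythm result, and the stated 95%/97% accuracy rests on an unstated rule for where those strips go

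*Protocol article*

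**What the plan says.** All references are to the protocol article.

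- **Results.** "As of March 1, 2024, a total of 2339 participants have been enrolled". "The KardiaMobile rhythm strip reported 381 abnormal readings, which are pending analysis from a cardiologist". The labels are then listed: "A total of 78 readings were labeled as possible AFib, 159 readings were labeled unclassified, and 49 were unreadable".
- **Discussion, limitations.** The article acknowledges "relatively high rates of unclassified or unreadable ECG outputs that have been included in the abnormal findings data". It adds that "the participants were not asked to return for another reading, as these outputs are representative of the device’s effectiveness".
- **Primary Measures, Detection Accuracy.** Unreadable and unclassified are two of the six device labels to be compared with the standard 12-lead ECG.
- **Procedure.** The accuracy analysis is reduced to two classes: "The number of positive screens versus negative screens will also be compared to assess the sensitivity and specificity". No class is given for a strip without a result.
- **Discussion, first paragraph.** "the study demonstrated KardiaMobile to have a sensitivity and specificity of 95% and 97" percent respectively, for AFib not previously diagnosed. No 2×2 table or denominator accompanies these figures.

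**The concern.** An unclassified or unreadable strip is neither a positive nor a negative AFib screen. Counting it as abnormal mixes device failure with rhythm findings, so the headline abnormal count says little about screening yield. The larger issue is accuracy, which is a primary measure. A two-class table must put these strips somewhere (positive, negative or left out), and the choice changes the specificity and the predictive value. The article publishes a count made under one rule beside accuracy figures whose rule is not given, and the Discussion uses those accuracy figures to support its cost-effectiveness conclusion.

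**Working it through.** **Inputs.** From Results: N = 2339; 381 abnormal; 78 possible AFib; 159 unclassified; 49 unreadable. From Discussion: sensitivity 0.95, specificity 0.97. From the Introduction: undiagnosed AFib of 0.9% (working-age adults) to 1.3% (older patients). Assumptions: one reading per participant, and the 78, 159 and 49 all lie within the 381.

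**Can 97% be reproduced?** No. The article gives no 2×2 table, so the figure can only be tested against possible counting rules.

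**Make-up of the 381.**
- No result: 159 + 49 = 208.
- Share of abnormal readings: 208/381 = 54.6%.
- Share of participants: 208/2339 = 8.9% (95% CI 7.8% to 10.1%).
- Other labels: 381 − 78 − 208 = 95, presumably tachycardia and bradycardia.
- Abnormal rate with no-results: 381/2339 = 16.3%. Without: (381 − 208)/2339 = 173/2339 = 7.4%.

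**Specificity under each rule.** With D AFib cases and P positive screens, specificity = 1 − (P − 0.95D)/(N − D). The cited rates give D = 0.009 × 2339 ≈ 21 and D = 0.013 × 2339 ≈ 30.

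| Counted as positive | P | D = 0 | 0.9% | 1.3% |
|---|---|---|---|---|
| All abnormal | 381 | 83.7% | 84.4% | 84.7% |
| Possible AFib plus no-result | 78 + 208 = 286 | 87.8% | 88.5% | 88.9% |
| Possible AFib only, all others negative | 78 | 96.7% | 97.5% | 97.9% |

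If the 208 are positive and none has AFib, they alone cap specificity at 1 − 208/2339 = 91.1%.

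**AFib cases needed for exactly 95%/97%.** Solve 0.95D + 0.03(n − D) = P, so D = (P − 0.03n)/0.92.
- P = 381, n = 2339: D = (381 − 70.2)/0.92 ≈ 338 (14.4%). False positives would be 0.03 × (2339 − 338) ≈ 60, so at least 208 − 60 = 148 of the no-results would have to be AFib.
- P = 286, n = 2339: D = (286 − 70.2)/0.92 ≈ 235 (10.0%), with at least 208 − 63 = 145 no-results being AFib.
- P = 78, n = 2339 (no-results counted negative): D = (78 − 70.2)/0.92 ≈ 8.5; true positives 0.95 × 8.5 ≈ 8.1; PPV 8.1/78 ≈ 10%.
- P = 78, n = 2339 − 208 = 2131 (no-results excluded): D = (78 − 63.9)/0.92 ≈ 15.3; true positives ≈ 14.5; PPV 14.5/78 ≈ 19%. This PPV is fragile: letting specificity run from 96.5% to 97.5% moves it from about 5% to 33%.

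**What excluding the strips would hide.** In the last case, true negatives are 0.97 × (2131 − 15.3) ≈ 2052. Put the 208 back as test failures in people without AFib, and specificity becomes 2052/(2131 − 15.3 + 208) = 2052/2323.7 ≈ 88.3%, a fall of about 9 points. The 91.1% cap is about 6 points below 97%.

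**The case against.** The strongest reply is that abnormal was never meant to equal AFib-positive. Detection Accuracy lists possible AF as a separate label, Procedure distinguishes screening as AFib from having an abnormal reading, and the 95%/97% is stated for AFib. The natural positive screen is then the 78 strips, and the table shows that about 97% fits. This stands. A count of abnormal labels and a specificity for AFib may properly use different definitions. Nor would counting the 208 as negative limit the figures to readable strips, since all 2339 stay in the denominator; only exclusion does that.

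A reader might therefore infer from the 208 strips that the 97% is impossible, or that it contradicts the 381. The documents do not support that. The impossibility holds only if abnormal is taken as positive, which the text does not say, and only if undiagnosed AFib is well below about 10% to 14%. At 16%, which the Introduction gives as total AFib prevalence in kidney patients not on dialysis, even 381 positives would allow 98.7%. That rate is not one for undiagnosed AFib across six clinics, so it is a weak escape, but it makes the claim conditional.

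Two further replies have some force. The article discloses the grouping and prints 78, 159 and 49 separately, so a reader can undo it. And the handling of indeterminate results is commonly left to an analysis plan; silence in Methods alone would not be a finding. Neither reply settles the matter. The article itself prints the accuracy figures as a demonstrated result, and the disclosure does not say how the 208 strips entered them. The article's own reason for not repeating readings, that such outputs reflect how the device performs, argues for keeping them visible in the accuracy assessment.

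**Conclusion.** The point holds as one of unstated and inconsistent handling, not of a disproved figure. It is certain that 208 of the 381 abnormal readings (54.6%) carry no rhythm result, and that removing them more than halves the abnormal rate, from 16.3% to 7.4%. Conditionally, treating abnormal as positive puts specificity at about 84-85% or 88-89% at the cited undiagnosed rates, whereas treating only the 78 as positive makes about 97% possible. The placement of these strips thus moves specificity by roughly 6 to 9 points or more, and the article does not state it. The rule behind the 97% must differ from the one behind the 381 unless undiagnosed AFib is far commoner than the article suggests.

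The 95%/97% is also premature on the article's own account, because the abnormal readings had not yet been analysed by a cardiologist.

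These sizes rest on one reading per participant and all 2339 in the denominator. The solved case counts and PPVs are illustrative only: participants with known AFib were not excluded, so some of the 78 may not be new cases.

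**What to change.** 1. Report three groups: possible AFib (78), other rhythm labels (the remaining 95, named), and no result (208).
2. Give the no-result rate with its 95% CI, 8.9% (7.8% to 10.1%), as a feasibility outcome.
3. Show the accuracy table against the 12-lead reference with no-results as their own row, and say how many of them have a reference result.
4. Give sensitivity and specificity twice: for readable strips only, and with no-results counted as test failures (a miss where AFib is present, a failure to clear where it is absent).
5. Withhold the 95%/97%, or mark it as provisional, until the table, the denominator and the cardiologist's readings are available.

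The cost is mainly re-tabulation of data already held. The downside for the authors is that the abnormal count and one version of specificity become less favourable.

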## Abbreviations

AFib: atrial fibrillation
ECG: electrocardiogram
HIPAA: Health Insurance Portability and Accountability Act
IRB: institutional review board
UF: University of Florida
